## Abstract

**Introduction:** Studies have shown that excess formaldehyde accumulation in the brain accelerates cognitive decline in people with Alzheimer’s disease (AD). Recently, reports from our research team revealed that red light treatment (RLT) improved memory in AD mice by activating formaldehyde dehydrogenase (FDH) and thus reducing formaldehyde levels. Here, we developed a medical RLT device to investigate the safety and efficacy of this device in older adults with mild to moderate AD.

**Methods:** This will be a randomized controlled trial (RCT) that will include 60 participants who will be recruited and randomly divided into an RLT group and a control group. The RLT group will receive RLT intervention 5 days a week for 30 min each time for 24 weeks while the control group will continue their routine treatments without RLT. All participants will undergo neuropsychological and functional assessments including the Mini-Mental State Examination, the AD assessment scale-cognitive subscale (ADAS-cog), the Geriatric Depression Scale (GDS), the Neuropsychiatric Inventory (NPI) and the Barthel Index at baseline, 12 weeks and 24 weeks. All participants will undergo functional magnetic resonance imaging (fMRI) scanning and blood/urine biomarkers tests at baseline and 24 weeks. The primary outcome will be the ADAS-cog score while the secondary outcomes will be the GDS and NPI scores. Adverse events will be recorded and treated when necessary. Both an intention-to-treat analysis and a per-protocol analysis will be performed to evaluate the safety and efficacy of RLT.

**Discussion:** This protocol outlines the objectives of the study and explained the RLT device developed by the research team. The study is designed as an RCT to evaluate the safety and effects of the RLT device on older adults with mild to moderate AD. This study will provide evidence for the clinical use of RLT on treatment for AD.

**Clinical Trial Registration:**
www.ClinicalTrials.gov, ChiCTR1800020163; Pre-results.

## Introduction

As the most common cause of dementia in the elderly, Alzheimer’s disease (AD) is becoming increasingly prevalent as the population ages. The Alzheimer’s Association has now estimated and reported that the number of people with AD in the world will be more than 130 million by 2050 (Alzheimer’s Association, 2019). The neuropathology of AD is characterized by the accumulation of β-amyloid (Aβ)-related amyloid plaques and phosphorylated tau (p-tau)-related neurofibrillary tangles outside and inside neurons, respectively. These changes are widely believed pathogenic to the onset of AD (Serrano-Pozo et al., 2011; Alzheimer’s Association, 2019). As a persistent, disabling, and costly disease, AD unavoidably puts a huge burden on the family and society (Jia et al., 2018). Unfortunately, over the past decades new medications targeting Aβ production, aggregation and clearance, and tau hyperphosphorylation, such as antibodies, vaccines, and small molecule medicines, have not resulted in desirable clinical efficacy (Lane et al., 2018).

Recently, as a non-pharmacological therapy, low levels of laser light have been found to disaggregate Aβ (Son et al., 2018); hence phototherapy targeting Aβ is being increasingly investigated as an alternative therapy for AD (Salehpour et al., 2018). Previous studies showed that endogenous formaldehyde (FA) concentrations were gradually accumulated in animals and humans during the aging process and that FA was abnormally elevated in AD patients (Tulpule and Dringen, 2013). Indeed, excess FA injection led to memory decline in healthy animal models (Tong et al., 2013, 2017; Wang et al., 2019). Notably, excess FA also directly induces Aβ aggregation (Chen et al., 2006, 2007; Rizak et al., 2014; Yang et al., 2014; Liu et al., 2018), tau protein phosphorylation and aggregation (Lu et al., 2013; Yang et al., 2014; He et al., 2017; Liu et al., 2018), and oxidative stress (Songur et al., 2008; MacAllister et al., 2011). These findings strongly suggest that disaggregation of Aβ by scavenging FA may contribute to the treatment of AD. Our recent studies found that red light at 630 nm improved cognitive function by activating formaldehyde dehydrogenase (FDH) and thus degrading FA and increasing catalase activity to reduce oxidative stress in senescence-accelerated mouse-prone 8 (SAMP8) mice (Zhang et al., 2019). Red light at 630 nm also reversed memory deterioration by de-aggregating Aβ and enhancing FA metabolism in amyloid precursor protein/presenilin-1 (APP/PS1) transgenic AD mice (Yue et al., 2019).

Based on the above experimental evidence in animal models, our research team developed a therapeutic device for people with AD by using light-emitting diodes (LED) with a 630-nm red light in 2015. The penetration of the LED red light at 630 nm has been previously tested and we found that 630 nm red light had a strong penetration rate into the human brain cortex (approximately 48%) and liver (approximately 68%; Yue et al., 2019). This device is made of three main parts, including a power control board, an LED helmet for transcranial irradiation of the head, and an LED belly band for transabdominal illumination of the liver (Figure 3), and works by reducing the body’s FA levels by activating FDH in the brain and liver. In this study, a 24-week randomized controlled trial (RCT) was designed to investigate the safety and efficacy of this therapeutic red light treatment (RLT) device on older adults with mild to moderate AD. This protocol is reported according to the Standard Protocol Items: Recommendations for Intervention Trials (SPIRIT) guidelines (Chan et al., 2013).

**Figure 1 F1:**
[figure not shown]
Schedule of recruitment, intervention, and assessment. Abbreviation: ADAS-cog, Alzheimer’s disease assessment scale-cognitive subscale; MMSE, Mini-Mental State Examination; NPI, Neuropsychiatric Inventory; GDS, Geriatric Depression Scale; BI, Barthel Index; fMRI, functional magnetic resonance imaging; FA, formaldehyde; FDH, formaldehyde dehydrogenase; Aβ, β-amyloid peptides; p-tau, phosphorylated tau protein.

**Figure 2 F2:**
[figure not shown]
Flow diagram of study design. Abbreviation: fMRI, functional magnetic resonance imaging.

**Figure 3 F3:**
[figure not shown]
The therapeutic device: a 630-nm red light device used for the treatment of AD patients. **(A)** The device is constructed of three main parts. From left to right, there is a power control board, an LED helmet for transcranial illumination of the head, and an LED belly band for transabdominal irradiation of the liver. **(B,C)** Images of the therapeutic illuminated LED lights in the “ON” position for treatment of AD patients. Abbreviation: LED, light-emitting diode.

### Objectives

The primary objectives are to test the safety and effects of the RLT on cognitive function, behavior/mood, and activities of daily living in older adults with mild to moderate AD.

The secondary objectives are: (1) to explore the changes in brain function by using functional magnetic resonance imaging (fMRI); and (2) to examine the changes in the levels or activities of blood/urine biomarkers, such as FA, Aβ, total tau, p-tau, and FDH.

## Methods

### Settings

This device was developed and this study was designed at the Beijing Institute of Brain Disorders, Capital Medical University, China. The recruitment, assessment, intervention, and follow-ups of participants will be conducted at the Center for Cognitive Disorders of Beijing Geriatric Hospital (BGH), China. The Case Report Forms will be filled and kept in BGH.

### Study Design

This is an RCT study with two parallel arms (1:1 allocation ratio): an intervention group receiving an RLT program and a control group receiving routine therapy without RLT treatment (Figures 1, 2).

### Recruitment of Participants

Participants will be recruited from the clinic, inpatient ward, or long-term care facilities near BGH. Residents who meet the inclusion criteria will be recruited.

### Inclusion Criteria

The inclusion criteria will be as follows: (1) 60 years old or older; (2) with a diagnosis of probable AD based on the National Institute of Neurological and Communicative Disorders and Stroke and the AD and Related Disorders Association (NINCDS-ADRDA) criteria (McKhann et al., 1984); and (3) with a clinical dementia rating score ≤2. If the participants are receiving cholinesterase inhibitors, memantine, or other dementia-related medications, they will have to take a therapeutic and stable dose for at least 3 months before screening.

### Exclusion Criteria

Participants will be excluded if they are experiencing any of the following conditions: (1) severe visual or auditory impairment; (2) serious medical conditions in major organs (such as the heart, lung, kidney, or liver) that limit the ability to participate in the study; (3) current alcohol or drug abuse; (4) any other conditions which may disturb assessments or interventions required in this study; (5) history of epilepsy; or (6) having been enrolled into any other interventional studies.

### Randomization and Allocation

Participants will be enrolled by dementia specialists. The randomization will be carried out by an independent research assistant who will not be involved in the enrollment, assessment, or intervention of the participants. Random number sequences will be generated using SAS software version 9.4 (SAS Institute Inc., Cary, NC, USA). Sealed envelopes with the serial number outside and group number inside will be produced and kept in a locked drawer that will be inaccessible to all the researchers. The envelopes will be opened sequentially by the independent research assistant after baseline assessments, and participants will be assigned to an intervention group and a control group at a ratio of 1:1 according to the group number printed inside the envelopes. Outcome evaluators and data analysts will be blinded to the group assignment.

### Interventions

In addition to their routine treatments and personalized daily care, participants in the RLT group will receive the 24-week intervention of RLT with a frequency of 5 days per week for 30 min each time. The RLT treatment will be performed by researchers or caregivers who are trained to operate the RLT device in advance. The participants will be put on the LED helmet and the LED belly band and receive RLT therapy with concurrent transcranial and transabdominal illumination in the morning (Figure 3). The light parameters of the RLT device are shown in Table 1. The researchers or caregivers will be asked to keep a strict watch over the participants during the intervention process. A form of RLT treatment schedule will be made for each participant in the RLT group. The researchers or caregivers who perform the RLT intervention will be asked to sign on the report form after every session of treatment to ensure compliance of the intervention.

**Table 1 T1:** Parameters of the therapeutic device of 630-nm red light for AD patients.

Source	The red light treatment device
Wavelength (nm)	630 ± 15
Power output per LED (mW)	5
Power density (mW/cm^2^)	20 (anterior helmet LEDs)
	40 (posterior helmet LEDs)
	5 (temporal helmet LEDs)
	5 (belly band LEDs)
Duration of each time (min)	30
Frequency of treatment	5 times per week

*Abbreviation: AD, Alzheimer’s disease; LED, light-emitting diode*.

Participants in the control group will continue their routine treatments and personalized daily care during the 24-week study period, including usual medicine, recreational therapy, and management of behavioral disorders following current guidelines. Except for the RLT intervention for the RLT group, all the other treatment strategies for the two groups will be the same.

### Demographic Data Collection

Demographic characteristics of all participants including age, gender, educational level, as well as medical history, medication list, and comorbidities will be documented.

### Neuropsychological Assessments

A set of neuropsychological tests will be used to assess cognitive function and behavior/mood of all the participants, and their activities of daily living will also be measured. The assessments will be performed at baseline, 12 weeks, and 24 weeks during the study period. (1) The Mini-Mental State Examination (Katzman et al., 1988) is the most frequently used assessment to measure global cognitive function. It is a 30-point scale that assesses orientation, memory, attention and calculation, recall, and language, with higher scores indicating better cognitive function. (2) The AD assessment scale-cognitive subscale (ADAS-cog; Chu et al., 2000) is a 12-item scale that primarily measures word recall, ability to follow commands, constructional praxis, naming, ideational praxis, orientation, word recognition, comprehension of spoken language, word-finding, language ability, and attention. The scores range from 0 to 75 and higher scores indicate greater cognitive impairment. (3) The Geriatric Depression Scale (GDS; Yesavage et al., 1982) is a short questionnaire to identify depression in older people and it is validated in mild to moderate dementia. (4) The Neuropsychiatric Inventory (NPI; Wang et al., 2012) is an assessment of 12 different behavioral and psychological symptoms common in AD. Each symptom is rated and scored according to the frequency and severity reported by the informants. The distress level of the caregivers associated with each symptom is also rated. (5) The Barthel Index (Mahoney and Barthel, 1965), is a 10-item, ordinal scale used to measure performance in activities of daily living. It is also performed by interviewing the caregivers.

### fMRI

fMRI is a non-invasive brain imaging technique to measure and map brain activity. In this study, we will collect the data of resting-state fMRI (rs-fMRI) for the analysis of neurophysiological changes (Lee et al., 2013; Smitha et al., 2017). Participants will receive fMRI scans by using a Philips Ingenia 3.0 T magnetic resonance system at BGH at baseline and 24 weeks. The following sequences will be acquired: (1) High-resolution anatomic images using a 3D T1-weighted inversion recovery turbo field echo sequence with the following parameters: repetition time (TR) 7.9 ms, echo time (TE) 3.5 ms, contiguous 180 sagittal slices of 1 mm thickness, flip angle 8°, 1 × 1 × 1 mm voxels, 160 × 210 × 180 matrices, and field of view (FOV) 160 × 211 × 180 mm. (2) Single-shot field echo echo-planar imaging sequence for rs-fMRI images with the following parameters: 200 sets of contiguous 40 transverse slices, 4 mm thickness, TR 3,000 ms, TE 35 ms, flip angle 90°, 2 × 2 × 4 mm voxels, 120 × 116 × 40 matrices, and FOV 240 × 240 × 160 mm. The total acquisition time of rs-fMRI is 609 s. During the scanning process, participants will be asked to keep their eyes closed and remain motionless.

### Blood/Urine Biomarkers

The biomarkers of blood and/or urine of all participants will be measured at baseline and 24 weeks. The concentrations of blood Aβ, total tau, and p-tau, which are related to the pathology of AD, will be quantified by human Aβ and tau ELISA kits. Meanwhile, blood and urine FA levels and blood FDH activity will be measured.

### Outcomes

The primary outcome will be the ADAS-cog score. The secondary outcomes will be the GDS and NPI scores. The safety of the RLT will be evaluated according to the incidence and severity of adverse events such as headache, dizziness, or nausea. The adverse events will be immediately reported, and handled by experienced physicians. Details of these possible adverse events and the treatments they receive will be recorded by filling in the case report forms. Physical examinations and necessary laboratory examinations, such as blood routine examination, liver function, and renal function, will be completed at baseline and the end of this study.

### Sample Size Calculation

No studies have investigated the effects of RLT treatment on people with AD. However, there have been relevant published literature that reported positive effects of photobiomodulation (PBM) with 810 nm near-infrared light on people with dementia. For example, PBM was shown to reduce ADAS-cog scores by 6.73 points after a 12-week consecutive treatment (Saltmarche et al., 2017), and by 5.18 points in another report (Chao, 2019). In this study, we anticipate at least an effect size of 0.48 in ADAS-cog scores after 24-week RLT intervention. The sample size was calculated using Power Analysis and Sample Size software version 15.0 (NCSS, LLC)^1^. A total sample size of 48 participants is sufficient to detect the target effect size with 90% power (*β* = 0.10) and a type I error of 5% (*α* = 0.05). Considering a dropout rate of 10%, a total of 54 participants is necessary. In this study, we intend to recruit 60 participants, with 30 participants in each group.

### Quality Control and Quality Assurance

At least three dementia specialists will work together to examine the participants and provide a diagnosis for each participant. All data will be monitored and reviewed by the principal investigator or research coordinators. Training will be provided to all researchers. Consistency coefficients in scoring assessment scales between researchers should be no less than 0.85. Data entry will be verified by a second researcher in the team. To protect participant confidentiality, only supervisors, researchers of this study, and the ethics committee will be authorized to access to the personal information and medical records of the participants.

### Statistical Methods

Statistical analysis of demographics and clinical characteristics will be performed using IBM SPSS Statistics for Windows, Version 20.0 (Release 2011, IBM Corp, Armonk, NY, USA). Continuous data will be reported as means ± standard deviations or 95% confidence intervals, and as numbers with percentage for categorical data. The difference in demographic and baseline characteristics between two groups will be analyzed by using the independent *t*-test, and a *chi*-square test will be used for categorical variables.

The main analysis method for the safety and efficacy of RLT intervention in this study will use the intention-to-treat analysis including all randomized participants (Hollis and Campbell, 1999). Besides, a per-protocol analysis will be performed on individuals who complete the total study (Sedgwick, 2015). The repeated measures of variance analysis will be used to examine variations of scores of neuropsychological tests over time between two groups. The association between intervention and incidence of adverse events will be analyzed using the *chi*-square test.

fMRI data will be preprocessed by using Statistical Parametric Mapping version 12.0 (The Wellcome Trust Centre for Neuroimaging at UCL, London, UK) on the MATLAB platform (Release 2013b, The MathWorks Inc, Natick, MA, USA). There are several critical steps including motion correction, slice timing correction, spatial normalization, and smoothing. After fMRI data preprocessing, the fractional amplitude of low-frequency fluctuation and functional connectivity analysis will be analyzed by using the REST software version 1.8 (Song et al., 2011).

The level of significance for statistical analysis will be set at 5% (*P* < 0.05). The researchers who perform the data analysis will be blinded to the allocation and the intervention.

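### Baseline differences between randomised arms are to be tested for significance, which cannot show whether an imbalance matters for ADAS-cog, while the outcome analysis names no prognostic covariate

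*Protocol article*

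**What the plan says.** The protocol article, Statistical Methods, plans significance tests on the baseline table. On continuous variables it says: "The difference in demographic and baseline characteristics between two groups will be analyzed by using the independent", naming Student's two-sample procedure. Categorical variables get chi-square tests. One threshold covers the whole analysis: "The level of significance for statistical analysis will be set at 5" per cent, with no exemption for baseline comparisons.

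The candidate variables appear elsewhere. Demographic Data Collection says: "Demographic characteristics of all participants including age, gender, educational level, as well as medical history, medication list, and comorbidities will be documented". Neuropsychological Assessments adds five scales measured at baseline (MMSE, ADAS-cog, GDS, NPI, Barthel Index). Blood/Urine Biomarkers adds six baseline measures (blood Aβ, total tau, p-tau, blood FA, urine FA, blood FDH activity). The article does not say which of these enter the baseline comparison.

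Randomization and Allocation describes a computer-generated sequence in sealed envelopes, opened by an independent assistant once baseline assessment is finished. Sample Size Calculation gives the size: "we intend to recruit 60 participants, with 30 participants in each group".

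For the scales, Statistical Methods plans a repeated-measures analysis of variance comparing the groups over time. It names no baseline covariate and does not link the baseline tests to that analysis.

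**The concern.** If allocation runs as described, the two arms are random halves of one sample. The null hypothesis of each baseline test is then true by design, and a small P value shows only that chance produced an unusual split. What matters for the trial is whether an imbalance lies in a variable that predicts ADAS-cog and is large enough to move the comparison. A P value answers neither part: it depends on sample size and takes no account of prognostic strength.

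In a trial of 60, this can mislead in two ways. Sizeable imbalances can pass as not significant. A table with many rows can also show a significant line when nothing is wrong. What is at stake is modest: how the baseline table is read, and whether the ADAS-cog analysis has protection against chance imbalance that was fixed in advance and does not depend on that table.

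**Working it through.** The article gives no operating figures for the baseline tests, so there is none to reproduce. The sample size figures are checked in step 4, because they decide whether an imbalance can be compared with the target effect.

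**Inputs**
- n = 30 per arm (Sample Size Calculation).
- Level 5% (Statistical Methods). The article does not state sidedness; two-sided is assumed.
- Number of tests k, not stated. Age, gender and education alone give k = 3. The six demographic and history items plus five scales give k = 11. Adding six biomarkers gives k = 17. History, medication and comorbidities count as one test each, which is an assumption.

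**1. Smallest imbalance that reaches significance**
- Continuous variable: t(0.975, 58) × √(2/30) = 2.002 × 0.258 = 0.517 SD. Anything smaller is not significant.
- Binary variable: 15/30 against 22/30 (50% v 73%) gives P = 0.063 by chi-square without continuity correction. 15/30 against 23/30 gives P = 0.032.

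**2. How often chance produces a notable imbalance that passes**
- P(|difference| > 0.3 SD) = 2 × (1 − Φ(0.3/0.258)) = 0.245 for any one variable.
- About 0.05 of this lies beyond 0.517 SD and would be flagged.
- Share that passes: (0.245 − 0.05)/0.245 ≈ 0.80, or about four fifths.

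**3. Chance of at least one spurious P < 0.05 in the table**
- Each single test flags chance 5% of the time.
- With k independent tests the probability is 1 − 0.95^k; the last column is simulated with a common correlation of 0.3.

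| k | Independent | Correlation 0.3 |
|---|---|---|
| 3 | 14.3% | 13.7% |
| 6 | 26.5% | 24.3% |
| 11 | 43.1% | 37.5% |
| 17 | 58.2% | 49.5% |

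**4. Can the 0.52 SD threshold be set against the target effect?**
- The article says "we anticipate at least an effect size of 0.48 in ADAS-cog scores after 24-week RLT intervention" and "A total sample size of 48 participants is sufficient to detect the target effect size with 90% power". The dropout step reproduces: 48/0.90 = 53.3, rounded up to 54.
- If 0.48 is a difference between two arms in SD units, 90% power needs about 92 per arm (184 in total), not 48. On this reading a baseline imbalance of 0.48 SD at 30 per arm gives P = 0.068 and passes narrowly.
- If 0.48 is Cohen's f for two groups, the total is 47.6, rounded to 48. Then d = 2 × 0.48 = 0.96, and an imbalance of that size gives P = 0.0005 and is flagged.
- A one-sample or paired t-test also gives 47.6, rounded to 48.
- The article does not say which reading applies, so the comparison with the target effect cannot be settled.

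**The case against.** The strongest reply is that nothing in the article depends on these tests. It does not say that comparability will be concluded from them, that non-significance will be reported as balance, or that a significant line will alter the model. Analysts are also to be blinded to allocation, which limits choosing covariates to favour one arm. All of this stands, and it keeps the point minor.

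Three stronger readings are tempting, and the documents support none of them.
- A reader might infer that the tests raise a false alarm in about half of trials. That needs some 13 or 14 independent tests (48.7% and 51.2%). The article lists no test set, and independence is doubtful because MMSE and ADAS-cog both measure cognition. Only a range can be given.
- A reader might infer that imbalances as large as the planned effect go unnoticed. This holds narrowly if 0.48 is in SD units and fails if it is Cohen's f.
- A reader might translate an imbalance into a stated bias in the ADAS-cog result. That needs a correlation the article does not give. A simple calculation would also assume an unadjusted comparison of levels, whereas the plan compares repeated measures over time and ADAS-cog is measured at baseline too. A group-by-time contrast depends on how a covariate relates to change.

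It can also be said that covariate lists are often left to a full protocol or SAP, which is not shown. That is fair, and the absence of a list is not itself the fault. The fault is the stated use of significance tests on randomised baseline data. The covariates belong to the remedy, because the tests cannot protect the comparison.

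**Conclusion.** The point holds and is minor. The article plans significance tests of baseline differences that, under its own allocation procedure, can only be chance. At 30 per arm and a two-sided 5% level, those tests leave unflagged any continuous imbalance below about 0.52 SD. Depending on how many variables are tested, they give at least one spurious flag with probability from about 14% (3 tests) to 58% (17 independent tests); positive correlation lowers these figures.

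Deleting the P values alone would change no result. The useful gain comes from fixing a few prognostic covariates in the ADAS-cog model, which adds precision and handles chance imbalance whether or not it is significant. The gain cannot be sized from the article, because it gives no correlations with ADAS-cog. The conclusion assumes that randomisation and concealment are carried out as described.

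**What to change.** In Statistical Methods:
- Replace the baseline t-tests and chi-square tests with a descriptive table by arm: mean and SD, median, or number and percentage as suits the variable, without P values.
- Prespecify the ADAS-cog model before unblinding. Use the 12- and 24-week scores as responses, baseline ADAS-cog as a covariate, and a small fixed set of variables already collected. Age and education (Demographic Data Collection) and the clinical dementia rating (Inclusion Criteria) are natural candidates.
- State that these covariates stay in whatever balance is observed, and that none is added or dropped because of a baseline P value.

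The cost is a few sentences of analysis wording and no new data. Beyond baseline ADAS-cog, the extra covariates use two or three degrees of freedom in a 60-person trial if each enters as a single term.

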## Ethics and Dissemination

This study protocol has been approved by the ethical review committee of the Beijing Geriatric Hospital (approval number: 2019-024). Information leaflets of the study will be available at the public area of the Center for Cognitive disorders of BGH. The leaflets will explain in full detail the aims and objectives of the study, selection criteria, and the processes that the study will be adhering to. The research team will provide an individual face to face consultation to all potential participants and their guardians to answer any questions they may have before signing the consent form. Informed consent will be obtained from all participants and/or their legal representatives. Participants will be allowed to withdraw from the study at any time and the reason for withdrawal will be recorded. The results of this study will be reported in peer-reviewed journals and presented at national or international conferences on aging and dementia.

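### The intention-to-treat analysis is declared on all randomised participants, but classical repeated-measures ANOVA, the only method named for the ADAS-cog, would omit anyone with a missing visit

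*Protocol article*

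**What the plan says.** The Outcomes section sets the endpoint: "The primary outcome will be the ADAS-cog score". The Neuropsychological Assessments section sets three time points: "The assessments will be performed at baseline, 12 weeks, and 24 weeks during the study period".

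The Statistical Methods section then makes three statements.

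- The main analysis of safety and efficacy "will use the intention-to-treat analysis including all randomized participants".
- In addition, "a per-protocol analysis will be performed on individuals who complete the total study".
- For the scores, "The repeated measures of variance analysis will be used to examine variations of scores of neuropsychological tests over time between two groups".

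The article does not say which analysis set the repeated-measures analysis uses or how a missing score enters it. Missing scores are expected: the Sample Size Calculation section allows for 10% dropout, and under Ethics and Dissemination "Participants will be allowed to withdraw from the study at any time and the reason for withdrawal will be recorded".

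**The concern.** Two choices in one paragraph do not fit together as written. The population is everyone randomised. The method, in its ordinary meaning, works on a complete row of three scores per participant and deletes any row with a gap. The per-protocol set is defined by completing the study, not by adherence to RLT, so under complete-case handling the two analyses would rest on nearly the same people.

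This matters because the two arms have different reasons to leave. RLT participants face 5 sessions a week for 24 weeks, which is 5 × 24 = 120 sessions. Controls face none, and there is no sham. Dropout that is unequal and related to response is therefore plausible. A completers comparison would then mix a treatment effect with a selection effect, and the per-protocol result, built on the same completers, would not reveal it.

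**Working it through.** **1. The plan's own figures.** The stated requirement is 48, with 10% dropout. 48 / (1 − 0.10) = 53.3, rounded up to 54, as stated. The 48 itself depends on how this is read: "we anticipate at least an effect size of 0.48 in ADAS-cog scores after 24-week RLT intervention". Read as Cohen's f = 0.48 (d = 0.96), a two-sample t-test at two-sided 0.05 needs 24 per arm, 48 in total, with power 0.902. A one-sample or paired reading also gives 48 (power 0.903). A between-group d of 0.48 does not: it needs 93 per arm, and 24 per arm gives power 0.37. The metric is a separate matter; here the 48 is taken as stated.

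**2. Who is analysed.** 60 are randomised.

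| Scenario | ANOVA set, no imputation | Completers (per-protocol) |
|---|---|---|
| 10% dropout (plan) | 60 × 0.9 = 54 | 54 |
| 20% dropout (assumed) | 60 × 0.8 = 48 | 48 |
| 10% dropout, 5% of completers miss only week 12 (assumed) | 54 × 0.95 ≈ 51 | 54 |

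At the planned rate 6 of 60 are omitted. The two sets coincide unless someone finishes the study but misses an earlier visit. In that case the ANOVA set is smaller still.

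**3. Power.** On the d = 0.96 reading, 27 per arm gives 0.933 and 30 per arm gives 0.955. Both are above the planned 90%.

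**4. Possible bias with no true effect.** All inputs here are assumed: ADAS-cog SD 10; the same correlation r between any two visits; dropout only in the RLT arm; and a fraction p dropping out, drawn as a random half of the 2p of participants with the worst 12-week change.

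- SD of change from baseline = 10 × √(2(1 − r)): 7.75, 6.32 and 4.47 at r = 0.7, 0.8 and 0.9.
- Mean standardised 12-week change among the worst 2p: 1.40 for p = 0.10 and 0.966 for p = 0.20 (upper tail of a normal distribution).
- Shift at 12 weeks among those who stay = p × that mean × SD of change / (1 − p).
- The correlation between the 12- and 24-week changes is 0.5 here, so the shift at 24 weeks is half as large.

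At r = 0.8 and p = 0.10: 0.10 × 1.40 × 6.32 / 0.90 = 0.98 points at 12 weeks and 0.49 at 24 weeks. At p = 0.20: 0.20 × 0.966 × 6.32 / 0.80 = 1.53 and 0.76.

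| RLT-arm dropout | r = 0.7 | r = 0.8 | r = 0.9 |
|---|---|---|---|
| 10% | 0.60 | 0.49 | 0.35 |
| 20% | 0.94 | 0.76 | 0.54 |

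The entries are the spurious 24-week benefit in points.

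**5. Size against noise.** At r = 0.8 and 10% dropout, the standard error of the difference in change is 6.32 × √(1/27 + 1/30) = 1.68, so the bias is 0.49 / 1.68 = 0.29 standard errors. At 20% it is 0.76 / (6.32 × √(1/24 + 1/30)) = 0.76 / 1.73 = 0.44. The two-sided error Φ(−1.96 + z) + Φ(−1.96 − z) is then about 0.060 and 0.073. Bias and standard error scale together, so this does not depend on r. A simulation with a different dropout rule (logistic in the 12-week change, r = 0.7) gave 0.055 and 0.074. In that simulation the complete-case difference was −0.04 and −0.09 SD, while an estimator using the 12-week data was off by only 0.006 and 0.004 SD.

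**The case against.** The strongest reply is that this is a condensed article. Declaring intention-to-treat on everyone implies some handling of missing scores, and the rule may stand in a full protocol or analysis plan that is not shown. That is fair as far as it goes, and it makes the consequence conditional. It does not remove the point, because the article itself fixed both the population and the method. A later plan would have to replace the ANOVA or put imputation in front of it for the population statement to be true.

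A reader might infer more than the documents support:

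- *That the intention-to-treat analysis simply is the per-protocol analysis.* This holds only if the classical ANOVA is meant, nothing is imputed, and no completer misses only week 12. The article states no complete-case rule.
- *That the choice of SPSS shows listwise deletion.* The package is named for demographics and clinical characteristics, not for the repeated-measures analysis, and it can also fit mixed models.
- *That stopping RLT ends follow-up.* Nothing says so. The Abstract and the Neuropsychological Assessments section apply the assessments to all participants, and the withdrawal sentence concerns leaving the study.
- *That the trial loses its power.* The plan claims that 48 is "sufficient to detect the target effect size with 90% power", and 54 expected completers exceed that.
- *That the safety analysis is affected.* The chi-square test on adverse events can include everyone randomised.

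It is also fair that the bias scenario is one-sided. Controls might leave too, session length and frequency were set from volunteers' feedback on tolerance, and outcome evaluators and analysts are blinded. The bias figures show what could happen; they are not a forecast.

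**Conclusion.** The point holds in a conditional form. As written, the declared population and the named method conflict for the primary outcome. With the classical ANOVA and no imputation, about 6 of 60 randomised participants would be missing from an analysis described as covering all of them, and the per-protocol analysis would offer little independent check.

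The possible distortion is modest: under the assumed one-sided dropout, a false benefit of about 0.35 to 0.6 ADAS-cog points at 10% RLT-arm dropout and 0.55 to 0.9 at 20%, with type I error of about 0.055 to 0.075 instead of 0.05. These sizes rest on an SD, correlations and a dropout mechanism that the article does not give. The count of 6 in 60 rests only on the plan's own dropout rate.

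**What to change.** For the intention-to-treat analysis, replace the repeated-measures ANOVA with a likelihood-based mixed model that uses every available visit. Treat the baseline, 12-week and 24-week ADAS-cog scores all as outcomes, with a common baseline mean in the two arms, and name the arm difference at 24 weeks as the primary contrast. The Randomization and Allocation section places randomisation after the baseline assessments, so everyone randomised should have a baseline score and be included. A model limited to participants with at least one post-baseline score would not achieve this, because it leaves out anyone lost before week 12.

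Multiple imputation before the planned ANOVA is an acceptable alternative. Both approaches assume that data are missing at random given the observed scores, so add one sensitivity analysis for departures from this, such as control-based imputation. Keep the completers analysis as secondary.

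The cost is a few sentences of analysis text and a little more analysis work, with no new visits or data. The change should be made before unblinding.
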